### Data integrity and analysis

The integrity of trial data will be monitored by regularly scrutinising data files for omissions and errors. We will perform double data entry of the primary and key secondary outcomes. The source of any inconsistencies will be explored and resolved. Electronic data will be stored on a secure server, and paper copies will be locked in a cabinet. Data will be accessible only by researchers, and participant confidentiality will be maintained through secure password-protected data storage during and after PAGPROS.

Data will be de-identified prior to statistical analysis, which will be performed on an ITT basis. Normality of data distribution will be assessed, and appropriate parametric (Student’s *t* test or analysis of variance) or non-parametric (Wilcoxon signed-rank test, Wilcoxon rank-sum tests) tests for between-group differences will be performed. Statistical significance will be assessed at *p* < 0.05. Subgroup analysis may be implicated and considered as PAGPROS develops. Time-to-event analysis will be undertaken using Kaplan-Meier estimates on the week 8 and week 18 VAS scores. Missing data will be handled by a single imputation method whereby the last observation will be carried forward and used as a surrogate for the missing value. This method is the favoured approach for replacing missing data because it is conservative, yields an appropriate estimate of variation in outcome and is unlikely to bias towards the alternative hypothesis [15]. An alternative approach to missing data may be use of a longitudinal mixed-effects model incorporated into the analyses.

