### Randomisation and blinding

The trial pharmacist (un-blinded) will generate a randomisation code using a computer-derived permuted block with varying block size sequence. Manufacturing and preparation of the medication capsules will be performed by an external good manufacturing practice-accredited facility. The unblinded pharmacist will be involved in the preparation of the medication kits as per the randomisation schedule. The sequence will follow a 2 × 2 sequential design whereby participants will receive PGB first, then GBP (or vice versa), in a double-blinded fashion. Owing to the variability in regular dosage frequency between the medications (PGB twice daily, GBP thrice daily), study medication packs will contain three bottles each, correlating to the dosage times of morning, lunchtime and night, so as to maintain blinding. Medication packs pertaining to the PGB arm will have placebo incorporated as the lunchtime dose with all medications being indistinguishable. The randomisation schedule will remain concealed from other researchers. Placebo capsules will have an appearance identical to the active capsules. The randomisation process will ensure concealed allocation and blinding of the specialist, the participant and the outcome assessor.

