### Data collection

Data collection will be conducted by the study researchers via telephone, email or online at baseline (before medication commencement) and at weeks 4, 8, 10, 14 and 18. Week 10 data collection will act as the cross-over secondary baseline for analysis purposes. Data will be entered into CRFs by dedicated trained staff. Each participant will receive up to seven face-to-face or telephone consultations with the trial pharmacist to commence treatment, monitor progress and adjust the dose of the study medication over the 8-week treatment periods. These visits will also incorporate a medical evaluation and collection of primary and secondary outcomes. Participants will receive usual neurosurgical care independent of and parallel to PAGPROS.

The use of prior and continued analgesic medicines will be collected at baseline. Adherence to study medication will be documented through a self-reported daily medication diary and by counting the returned medicine compared with the prescribed regimen as recorded by the trial pharmacist. Participants will be asked to return used and unused study medications at each visit.

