### Sample size

We hypothesise that over an 8-week treatment period, GBP will reduce pain on the VAS scale by an average of 4.5 points from (7.5 to 3.0) as per historical literature [16]. We predict PGB to show at least the same benefit. We hypothesise that PGB will display superiority over GBP by at least a 20% better relative reduction in VAS score, with a resultant reduction of 5.4 (from 7.5 to 2.1) points from baseline. This 20% relative reduction is based on the average reduction of pain symptoms compared with placebo for indirect comparisons [1, 16]. Relative reduction will be used because it is often more impressive and also to allow for the instance of a lower-than-expected event rate, which would lower the absolute risk reduction.

If the true difference in means of both arms of the study is 0.9 with an SD of 1.2, in order to detect this 20% relative decrease in pain between GBP and PGB, we will need to study 30 patients (15 per treatment arm) to reject the null hypothesis with 80% power. The type I error probability associated with this test of the null is 0.05. Assuming a 20% drop-out rate, the total sample size will be 38 patients (19 per treatment arm). We have chosen this large effect size and conservative SD on the basis of anecdotal and specialists’ experience with this cohort of patients. The benefits of the cross-over methodology are evident with the small sample size required, owing to each participant acting as his/her own control. If this were a conventional parallel study design, the sample size needed would be approximately 100 participants. We conservatively estimate that if two people can be recruited per week, the study duration will be approximately 1.5 years.

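### The listed tests do not commit the primary comparison to the within-patient analysis on which the sample size of 30 (38 with drop-out) depends, and the stated reason for using relative reduction does not fit a continuous VAS

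*Protocol article*

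**What the plan says.** The protocol article's Randomisation and blinding section describes a 2 × 2 design in which each participant takes both drugs, in one order or the other.

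Its Sample size section assumes: "If the true difference in means of both arms of the study is 0.9 with an SD of 1.2". It concludes that "we will need to study 30 patients (15 per treatment arm) to reject the null hypothesis with 80% power", and adds that "The type I error probability associated with this test of the null is 0.05". With 20% drop-out the total becomes 38. The small number is said to be possible "owing to each participant acting as his/her own control", and a parallel trial is put at about 100 participants.

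The Data integrity and analysis section plans an assessment of normality, then either Student's t test or ANOVA, or "non-parametric (Wilcoxon signed-rank test, Wilcoxon rank-sum tests) tests for between-group differences will be performed". A mixed-effects model appears only as a possible alternative for missing data. No period or sequence term is stated.

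The Data collection section adds: "Week 10 data collection will act as the cross-over secondary baseline for analysis purposes". On the effect scale, the Sample size section says: "Relative reduction will be used because it is often more impressive". It gives as a further reason protection against a low event rate that would shrink the absolute risk reduction.

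**The concern.** The sample size section counts on comparing each patient with himself or herself. The analysis section does not secure that comparison. It puts a paired test (signed-rank) beside a two-sample test (rank-sum), leaves the pairing of the t test open, and does not define the groups. The normality check formally chooses between parametric and non-parametric tests. Because pairing is fixed in neither branch, that check can also change whether the comparison is within patients.

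Two things are at stake. First, an analysis that the text permits would miss the planned 80% power. Second, a paired test that leaves out period takes any change between weeks 8 and 18 into its error, and into its estimate if the two sequences are not equally represented.

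The effect scale is a separate weakness. An outcome measured in VAS points has no event rate and no absolute risk reduction, and the calculation is built on an absolute difference.

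**Working it through.** **Inputs.** From the Sample size section: difference 0.9, SD 1.2, 30 completers, 80% power, alpha 0.05, 38 with drop-out, about 100 if parallel. Two assumptions are needed, because the article states neither: the test is two-sided, and 1.2 is the within-patient SD. Both are supported by the reproduction in step 1.

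**1. The plan's own figure.** SD of a within-patient difference = 1.2 × √2 = 1.697. Noncentrality at n = 30 = 0.9 / (1.697/√30) = 2.90. The noncentral t distribution with 28 df gives power 0.801, and 30 is the smallest n that reaches 0.80. Drop-out: 30/0.8 = 37.5, so 38. Other readings fail:
- 1.2 as the SD of the difference needs 16–17 patients by t, or 14 by the normal approximation.
- Two independent groups with SD 1.2 need 28–29 per arm, or 56–58 in total.

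So 30 is a within-patient number.

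**2. Correlation implied by the parallel figure of 100.**
- If 100 excludes drop-out: total SD = 0.9 / [(1.96 + 0.842) × √(2/50)] = 1.606, and ρ = 1 − 1.44/1.606² = 0.44. The ratio formula 2 × 30/(1 − ρ) = 100 gives 0.40.
- If 100 includes drop-out, as the 38 does: 2 × 38/(1 − ρ) = 100 gives ρ = 0.24.

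**3. Two-sample t test of 30 PGB values against 30 GBP values, pairing ignored.** The total SD is 1.2/√(1 − ρ). The test uses a standard error of total SD × √(2/30). The true standard error of the mean difference is 1.2 × √(2/30) = 0.310. The critical t with 58 df is 2.002.

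| | ρ = 0.44 | ρ = 0.24 |
|---|---|---|
| Total SD | 1.604 | 1.376 |
| Standard error used by the test | 0.414 | 0.355 |
| Difference needed for significance | 0.829 | 0.711 |
| Power | Φ[(0.9 − 0.829)/0.310] = 0.59 | Φ[(0.9 − 0.711)/0.310] = 0.73 |
| Type I error | 2[1 − Φ(0.829/0.310)] = 0.007 | 2[1 − Φ(0.711/0.310)] = 0.022 |

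Simulation, which lets the standard error vary, gives similar power and type I error of about 0.01 to 0.03. Over a wider assumed range, power is 0.75 at ρ = 0.2, 0.53 at 0.5 and 0.40 at 0.6.

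**4. Paired t test with no period term, 15:15.** With a period difference π, the PGB − GBP difference has mean 0.9 − π in one sequence and 0.9 + π in the other, so the pooled variance is inflated by about π². The values of π are assumed.

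| Assumed π (points) | Power, no period term | Power, period-adjusted |
|---|---|---|
| 0 | 0.80 | 0.80 |
| 0.5 | 0.78 | 0.80 |
| 1 | 0.70 | 0.80 |

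**5. Unequal sequences.** The unadjusted paired estimate is shifted by π × (difference in sequence sizes)/N. For an assumed 18:12 split and π = 1, the shift is 1 × 6/30 = 0.20. The estimate becomes 0.70 or 1.10 instead of 0.90, depending on which sequence is smaller. The period-adjusted estimate stays at 0.90.

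**The case against.** The strongest reply is that the text allows a correct analysis. Signed-rank is paired, and ANOVA can carry treatment, period, sequence and patient. A t or rank-sum test applied to within-patient period differences, compared between sequences, is a standard period-adjusted cross-over test. In simulation at 15:15 it keeps about 0.80 power (t) and 0.77 (rank-sum), whatever the period effect. The article is condensed, and a fuller plan may settle the model. All of this stands. A reader might infer that own-control power is lost, or that no period term will be fitted. The documents support only that the power is not secured and that no period term is stated.

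Other stronger readings also go too far:

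- **Large period effects.** A period effect of 2 points would cut the power of the unadjusted paired test to 0.40, but no figure in the article supports an effect that large. At 0.5 points the loss is trivial.
- **Bias from unequal drop-out.** The plan is intention-to-treat with last observation carried forward, which keeps drop-outs in the analysis. The 18:12 split is therefore an illustration and not a prediction.
- **Subtracting the week-10 baseline.** A reader might infer that change scores raise the SD of the difference to 2.4. The article calls week 10 a baseline but does not say it is subtracted. The 0.9 is itself a difference between reductions (5.4 v 4.5), so 1.2 may already be a change-score SD.
- **Relative reduction as a cause of lost power.** The choice of scale does not affect the own-control gain.
- **False positives.** The unpaired comparison is conservative, so the risk is a missed difference.

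What remains is that the published wording permits an analysis that does not deliver the published power, and nothing in it selects the valid versions.

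**Conclusion.** The point holds as a failure to commit. The 30 patients give 80% power only with a within-patient comparison, and the stated tests do not require one. Used on the drug groups, the two-sample option has about 59–73% power and a type I error of about 0.01–0.03. That range comes from the article's own parallel figure of 100, read without or with drop-out. A paired test with no period term is adequate unless the period effect is sizeable, and it is biased only if there is a period effect and the analysed sequences are unequal.

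These figures assume a two-sided test, 1.2 as the within-patient SD and 30 completers. The sizes of the period effect and of the sequence imbalance are illustrative.

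The reason given for relative reduction is wrong for this outcome, whatever a fuller plan says. Impressiveness is not a ground for choosing an effect measure, event-rate language does not apply to a continuous VAS, and the trial is sized on an absolute 0.9 points.

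**What to change.** - Name one primary analysis of end-of-period VAS (weeks 8 and 18) that is within-patient and period-adjusted. One option is a mixed model with treatment, period and sequence as fixed effects and patient as random. With complete data, the equivalent is a two-sample t test on within-patient period differences, compared between sequences.
- Keep the rank-sum version of that same test as a sensitivity analysis, and say that the groups it compares are the sequences.
- Do not let a normality pre-test choose between paired and unpaired tests.
- Report the absolute mean VAS difference with 95% CI as the primary effect.
- Delete the sentence saying that relative reduction will be used.

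The cost is wording and one degree of freedom for period: power at 30 completers is 0.802 with 29 df and 0.801 with 28 df. No new data or patients are needed. The change should be made before unblinding.

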## Background

Sciatica or sciatic neuralgia, a common form of lumbosacral radiculopathy, is characterised by low back pain which radiates to the leg and which may be accompanied by sensory loss, motor weakness and/or reflex abnormalities. Sciatica is a symptom defined as well-localised leg pain with a sharp, shooting or burning quality that approximates to the dermatomal distribution of the sciatic nerve down the posterior lateral aspect of the leg [1]. It is often associated with numbness or paraesthesia in the same distribution but typically extends beyond the limits of perceived pain in either a dermatomal or sclerotomal anatomical fashion [2, 3]. The term *sciatica* is used by clinicians in different ways: Some refer to any leg pain referred from the back as sciatica; others prefer to restrict the term to pain originating from the lumbar nerve root. Others believe sciatica is a form of ‘neuropathic’ pain caused by compression or irritation of the roots or nerves that comprise the sciatic nerve [1, 4]. Chronic sciatica (CS) is sciatica which has been present for more than 3 months despite active conservative management, including physical therapy. CS may complicate previous chronic low back pain; however, it may also present purely as an isolated phenomenon [1, 4].

The annual prevalence of sciatica varies widely (1.6–43%) with male predominance [4]. Sciatica accounts for 5% of patients with low back pain presenting to primary care practices and 30% have persistent pain for longer than 12 months. Of these 30% presenting to primary care, 20% are already out of work, and 5–15% require surgery. Over half of patients with sciatica will have pain 4 years post-diagnosis, and the socio-economic cost per country per year is estimated to be $128 million for in-hospital care, $730 million for absenteeism and $708 million for disability [5].

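### The listed tests do not commit the trial to a within-patient, period-adjusted comparison, although the sample size depends on one

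*Protocol article*

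**What the plan says.** The protocol article's Randomisation and blinding section sets a two-sequence, two-period cross-over: "participants will receive PGB first, then GBP (or vice versa), in a double-blinded fashion". Allocation uses a "computer-derived permuted block with varying block size sequence".

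Sample size states "If the true difference in means of both arms of the study is 0.9 with an SD of 1.2" and concludes "we will need to study 30 patients (15 per treatment arm) to reject the null hypothesis with 80% power", at a type I error of 0.05. It credits the small number to the cross-over, "owing to each participant acting as his/her own control", and puts a parallel trial at about 100 participants. A 20% drop-out allowance takes 30 to 38.

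Data integrity and analysis then says that normality will be assessed and that either parametric tests (Student's t or analysis of variance) or "non-parametric (Wilcoxon signed-rank test, Wilcoxon rank-sum tests) tests for between-group differences will be performed". It does not say whether the t test is paired, which Wilcoxon test compares the drugs, or what terms the analysis of variance has. A mixed-effects model appears only as a possible alternative for missing data.

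**The concern.** In a 2×2 cross-over the efficient and unbiased comparison uses each patient's own difference and removes any general change between the first and second period. The protocol does not leave its tests to a later document: it names a menu, and the menu mixes a paired procedure (signed-rank) with an unpaired one (rank-sum) under a single description.

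An analyst could comply with the text and still do either of two unsuitable things:

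- pool all PGB scores and all GBP scores and compare them as independent samples, which discards the pairing that the sample size relies on; or
- run a paired test with no period term, which puts any period shift into the error and, if the sequences are unequal, into the drug contrast.

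Several p-values for the main efficacy comparison would all be within plan.

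**Working it through.** **Inputs.** From Sample size: difference 0.9, SD 1.2, 30 evaluable patients, 80% power, alpha 0.05, about 100 for a parallel design. The test is taken as two-sided because the primary objective allows either drug to be superior. Assumed, because the document gives no figure: the type of SD, the within-patient correlation ρ, the period shift π (period 2 minus period 1) and the final split by sequence.

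**1. Reproducing n = 30.** Take 1.2 as the within-patient SD. The SD of a paired difference is 1.2 × √2 = 1.697, and the noncentrality is 0.9 / (1.2 × √(2/30)) = 2.905. Noncentral t power is 80.2% for a paired t test (29 df) and 80.1% for the period-adjusted cross-over test (28 df). Drop-out: 30 / 0.8 = 37.5, so 38. The stated figures are reproduced. Reading 1.2 as the SD of the paired difference does not reproduce them (about 16 patients would be enough). Reading it as the total SD in an unpaired comparison of 30 against 30 scores gives 81.5%, so that reading also fits.

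**2. Implied correlation.** For a parallel trial with m per arm, total SD = 0.9 × √(m/2) / (1.960 + 0.842).

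- m = 50: 0.9 × 5 / 2.802 = 1.606; ρ = 1 − (1.2/1.606)² = 0.44.
- m = 40 (if the 100 includes 20% drop-out): 0.9 × 4.472 / 2.802 = 1.437; ρ = 0.30.

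**3. Pairing ignored.** The two-sample t test uses a standard error too large by 1/√(1 − ρ), so its critical value of 2.002 acts as 2.002/√(1 − ρ).

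- ρ = 0.44: 2.679; power ≈ P(Z > 2.679 − 2.905) = 59%.
- ρ = 0.30: 2.396; power ≈ P(Z > 2.396 − 2.905) = 69%.

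Simulation (no period effect):

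| ρ | two-sample t | pooled rank-sum |
|---|---|---|
| 0 | 82% | 80% |
| 0.30 | 69–70% | 66–67% |
| 0.44 | 59% | 55% |
| 0.70 | 25% | 23% |

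Actual type I error is about 1% at ρ = 0.44 and 2% at ρ = 0.30. If 1.2 is the total SD, the two-sample t test has 81% to 94% power for ρ from 0 to 0.7.

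**4. Period ignored, sequences 15/15.** The mean difference stays unbiased, but its estimated variance rises from 2.88 to 2.88 + π² × 30/29. For π = 1.0 the critical value 2.045 acts as 2.045 × √(3.914/2.88) = 2.384; power ≈ P(Z > 2.384 − 2.905) = 70%. Simulation:

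| π | paired t | signed-rank | period-adjusted t | rank-sum on period differences |
|---|---|---|---|---|
| 0 | 80% | 78% | 80% | 77% |
| 0.5 | 78% | 76% | 80% | 77% |
| 1.0 | 70% | 67% | 80% | 77% |
| 1.5 | 57% | 51% | 80% | 76% |

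**5. Period ignored, unequal sequences.** The bias of the paired estimate has size π × (n₁ − n₂)/N. For π = 1.0: 4/30 = 0.13 at 17/13 and 8/30 = 0.27 at 19/11, which are 15% and 30% of the 0.9 target. Type I error of the paired t test is then about 4% and 8%. When the bias runs against the true effect, its power is 54% and 39%, against 79% and 77% for the period-adjusted test.

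**The case against.** The strongest reply is that the menu contains valid choices. Analysis of variance with patient, period and drug terms handles both pairing and period. A rank-sum test on within-patient period differences, compared between the two sequences, is a standard cross-over test and is properly a comparison of groups. The reliance on self-control in Sample size, and the week-10 second baseline in Data collection, suggest that the authors meant a within-patient analysis. This stands, and a reader should not infer that every named test fails. What remains is that the text selects none of these uses and equally admits the unsuitable ones.

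A reader might also infer that a sizeable period effect is likely because "30% have persistent pain for longer than 12 months". That figure describes primary-care patients. The trial enrols chronic sciatica at a tertiary clinic, and the same section says over half still have pain at four years. The remark on tolerance under Treatment duration concerns side effects, not pain. Usual neurosurgical care does run in parallel, but other pain interventions lead to withdrawal. The documents therefore do not establish a pain period effect, and the 1.0 and 1.5 shifts exceed the 0.9 target difference.

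Two further limits stand. Blocked allocation, with intention-to-treat analysis and carried-forward values, may keep the analysed sequences near equal, which would remove most of the bias but not the power loss. Analysing change from each period's own baseline would remove a shift already present at week 10.

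**Conclusion.** The point holds as a failure to commit, not as a demonstration that the trial will be analysed wrongly. Pooled unpaired testing would leave about 55–60% power (about 66–70% if the parallel figure includes drop-out), provided that 1.2 is the within-patient SD; under the total-SD reading there is no loss against 80%. Paired testing without a period term costs little at a 0.5-point shift and becomes serious at 1.0 or more. Its bias needs both a real shift and unequal analysed sequences. It would be tempting to say that the design loses much of its power whichever test is used, or to illustrate bias with a 20/10 split. The first is contradicted by the valid uses of the listed tests, and the second needs more patients in one sequence than the 19 planned. The correlation, the period shift and the final split are all assumptions. Because the choice decides the primary result, it should be settled before unblinding.

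**What to change.** Name one primary analysis: a cross-over analysis of variance or linear mixed model with drug and period as fixed effects and patient as a random effect. As the non-parametric back-up, name the rank-sum test on within-patient period differences compared between sequences. Remove pooled unpaired PGB-versus-GBP tests and the unadjusted signed-rank test as options for the primary comparison. State in Sample size whether 1.2 is the within-patient SD, the total SD or the SD of the paired difference.

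The cost is wording and one degree of freedom: power moves from 80.2% to 80.1% if there is no period effect. No new data or patients are needed.

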### Objectives

#### Primary objective and outcome

Our primary objective is to demonstrate if either GBP or PGB demonstrates superiority over the other in terms of efficacy for the treatment of patients diagnosed with CS. The co-primary outcome is leg pain intensity using a visual analogue scale (VAS) measured at baseline and at weeks 4, 8, 10, 14 and 18. The participants will be asked to rate their average leg pain over the last 24 h on a scale of 10, with zero representing ‘no leg pain’ and 10 representing the ‘worst pain imaginable’ [10].

The co-primary outcome is the Oswestry Disability Index (ODI) [10], measured at baseline and at weeks 4, 8, 10, 14 and 18, to assess disability. The Health Locus of Control Scale (HLOC) will also be used at baseline and at weeks 4, 8, 10, 14 and 18 to assess participants’ decision-making processes because we have identified compliance with these medications as being low [10].

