### Study treatment

Participants will be randomised to commence treatment on either PGB or GBP. As a result of the cross-over methodology, participants will have the opportunity to experience both PGB and GBP, and we predict little or no carry-over effects (medium- or long-term) after the washout period. We believe the incorporation of a stand-alone placebo arm is unethical in trials where participants with moderate to severe pain are recruited.

The starting dose of PGB is 150 mg once daily for the first week. This will be titrated to the participant’s optimal dose up to a maximum of 300 mg twice daily, depending on their progress and tolerance at each dose level. The starting dose for GBP is 400 mg once daily for the first week. This will be titrated to the participant’s optimal dose up to a maximum of 800 mg thrice daily, depending on their progress and tolerance at each dose level. These doses are based on national recommendations from the Australian Medicines Handbook [11]. In the standard study dosing regimen (Table 1), we expect a 4-week titration period, after which the maximum tolerated dose for each participant will be maintained for 4 weeks before the first study medication is ceased in preparing for washout. The washout period between treatment phases will last 1 week, which is sufficient for these medications because they possess a short half-life (5–7 h). The dosage of either PGB or GBP can be amended at any stage in PAGPROS on the basis of efficacy and/or SEs by communication between the study specialist and the study pharmacist. The maximum treatment period is 8 weeks [13].

**Table 1 Tab1:** PAGPROS medication titration schedule

	Medication	Total daily dose
Week	Pregabalin	
1	1 × 150-mg capsule in the morning	150 mg/day
2	1 × 150-mg capsule three times daily (middle dose is placebo)	300 mg /day
3–8	2 × 150-mg capsules three times per day (middle dose is placebo)	600 mg/day
Week	Gabapentin	
1	1 × 400-mg capsule in the morning	400 mg/day
2	1 × 400-mg capsule three times per day	1200 mg/day
3–8	2 × 400-mg capsules three times per day	2400 mg/day

*PAGPROS* Pregabalin and Gabapentin Prospective Clinical Trial for the Treatment of Sciatica: A Randomised, Double-Blind, Cross-over Study

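### The Kaplan-Meier analysis is applied to pain scores taken at one fixed visit per period, so it can give only a responder proportion and uses no time information

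*Protocol article*

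**What the plan says.** The sentence at issue is in the Protocol article, Data integrity and analysis: "Time-to-event analysis will be undertaken using Kaplan-Meier estimates on the week 8 and week 18 VAS scores".

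The rest of the article shows what those scores are:

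- **Type of outcome** (Primary objective and outcome). Participants "rate their average leg pain over the last 24 h on a scale of 10". This is a co-primary outcome.
- **Timing** (same section). It is "leg pain intensity using a visual analogue scale (VAS) measured at baseline and at weeks 4, 8, 10, 14 and 18", on the same schedule for everyone.
- **Period length** (Study treatment). "The maximum treatment period is 8 weeks", so week 8 closes the first period.
- **Second baseline** (Data collection). "Week 10 data collection will act as the cross-over secondary baseline for analysis purposes", so week 18 closes the second period.
- **Design** (Randomisation and blinding). In the 2 x 2 scheme "participants will receive PGB first, then GBP (or vice versa), in a double-blinded fashion".
- **Other planned tests** (Data integrity and analysis). These are Student's t test or analysis of variance, or "non-parametric (Wilcoxon signed-rank test, Wilcoxon rank-sum tests) tests for between-group differences will be performed".
- **Sample size.** It is based on a difference in mean VAS: "If the true difference in means of both arms of the study is 0.9 with an SD of 1.2".

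The article gives no VAS event, time origin or censoring rule.

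**The concern.** Kaplan-Meier estimation is for data in which each person has a time to an event, the times vary between people, and some are censored. The sentence supplies two pain ratings instead, each read at a visit fixed in advance. Nothing varies in time.

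This is not a detail left for a statistical analysis plan. Such a plan could supply the missing event definition, but while the inputs remain the week 8 and week 18 scores, no definition restores information about time.

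Two things are at stake. A prespecified analysis of a co-primary outcome would look like survival evidence but contain only a proportion, and that proportion depends on a threshold not yet chosen. The pairing of week 8 with week 18 also invites a contrast of the two weeks, which in this design is not a contrast of the drugs.

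**Working it through.** **1. What the design rests on.** Inputs from Sample size: difference 0.9, SD 1.2, 80% power, type I error 0.05 (two-sided assumed), 20% drop-out. If 1.2 is the SD of a single score and a patient's two scores are taken as uncorrelated, the SD of the within-patient difference is 1.2 x √2 = 1.697. A paired t test then needs n = 30 (power 0.802), and 30 / 0.8 = 37.5, rounded up to 38. The article's 30 and 38 are reproduced. The article does not say which SD is meant; if 1.2 were the SD of the difference, the same test would need 16. Either way the calculation concerns means, with no event count or hazard ratio.

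**2. What Kaplan-Meier gives with one reading per period.** Suppose an event is VAS at or below some threshold, read at the end-of-period visit (an assumption; no threshold is stated). For one drug in one period let n be the number still observed at that visit and d the number of responders. There is one event time, so

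S(8) = 1 − d/n.

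This is one minus the responder proportion. Anyone censored earlier is simply absent from n. Since the same section fills missing values by carrying the last observation forward, there would be little or no censoring.

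**3. Numerical check.** One simulated data set used the protocol's end-of-treatment means (PGB 2.1, GBP 3.0), SD 1.2 and normal scores, with 38 readings per drug treated as independent and threshold VAS ≤ 3. Responders were 32 of 38 (PGB) and 18 of 38 (GBP), 50 of 76 in all.

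- Expected PGB responders under no difference: 38 x 50 / 76 = 25.
- Variance: 38 x 38 x 50 x 26 / (76² x 75) = 4.333.
- Log-rank: (32 − 25)² / 4.333 = 11.31.
- Pearson chi-square: 76 x (32 x 20 − 18 x 6)² / (38 x 38 x 50 x 26) = 11.46.
- 11.46 x 75/76 = 11.31.

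The log-rank statistic is the 2x2 chi-square apart from the factor (n − 1)/n.

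**4. Dependence on the threshold.** Expected responder proportions under the same means, SD and normality:

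| Assumed threshold | PGB | GBP | Difference |
|---|---|---|---|
| VAS ≤ 2 | 0.467 | 0.202 | 0.265 |
| VAS ≤ 3 | 0.773 | 0.500 | 0.273 |
| VAS ≤ 3.75 | 0.915 | 0.734 | 0.181 |

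**5. Week 8 against week 18.** With 19 participants per sequence, each week has 19 on each drug. With no period or carry-over effect, the expected mean is (2.1 + 3.0)/2 = 2.55 at both weeks, and the expected proportion at VAS ≤ 3 is (0.773 + 0.500)/2 = 0.64 at both. The assumed drug difference of 0.9 cancels, so a contrast of the weeks estimates a period effect.

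**The case against.** The best defence is that the sentence is loosely worded and does little harm. Several parts of it stand.

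- **The comparison is not invalid.** Both drugs are present at week 8 and at week 18, one per sequence. Responder proportions by drug within a period are a legitimate randomised comparison, though an inefficient one. A reader might infer that Kaplan-Meier here cannot compare the drugs at all; the design does not support that.
- **Risk-set bias is not established.** A reader might infer that responders at week 8 leave the risk set before taking their second drug. That would follow if both weeks were placed on one time axis, but the article does not say so, and the week 10 secondary baseline suggests that the clock restarts. I therefore put no figure on such a loss.
- **No extra significance test is stated.** A reader might infer a further test at p < 0.05, or a log-rank test that ignores the pairing. The sentence names estimates only, and the significance level follows the parametric and non-parametric tests.
- **More readings exist.** VAS is also taken at weeks 4 and 14, so each drug has two on-treatment readings. Using them would give two possible event times per period, still coarse, but the sentence names only weeks 8 and 18.
- **Event definitions often sit in the analysis plan.** That is fair, and their absence is not the point here.

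What the defence does not answer is that the named inputs carry no time information under any event definition.

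**Conclusion.** The point holds in a limited form. The article names the wrong kind of data for the method: a fixed-visit score at the end of each period can give only a responder proportion, whatever threshold is chosen. This follows from the visit schedule and needs no numerical assumption. The proportions and test statistics in the working are illustrations that assume normal scores, the protocol's means, SD 1.2 for a single score, and thresholds the article does not give.

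The consequence is an uninformative analysis of a co-primary outcome, open to misreading if the two weeks are contrasted. Loss of responders from the risk set remains a conditional hazard, arising only under a single time axis. The mean VAS comparison and the 30 and 38 patients are untouched, so this is a correction worth making and not a threat to the trial's main result.

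**What to change.** Delete the Kaplan-Meier sentence. In its place, state that week 8 and week 18 VAS are the two end-of-period outcomes and will be compared within patient, with treatment and period effects. In simplest form, take each participant's week 8 score minus week 18 score and compare these differences between the two sequences; half the contrast is the drug effect free of period. With the protocol's means the expected differences are 2.1 − 3.0 = −0.9 (PGB first) and 3.0 − 2.1 = +0.9 (GBP first), so half the contrast is (−0.9 − 0.9)/2 = −0.9, the difference the sample size assumes. This fits the families of tests already listed.

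If a responder summary is wanted, fix the threshold in advance and compare end-of-period proportions within patient by drug, using McNemar's test or, to allow for period, conditional logistic regression with a period term.

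The cost is one replaced sentence, best recorded before unblinding. It needs no new data or visits and does not change the sample size.
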